### 5.4 Definition of Dose-Limiting Toxicity (DLT) and Maximum Tolerated Dose (MTD)

Dose limiting toxicities (DLTs) are defined as the following possibly, probably, or definitely related study drug toxicities:

- $\geq$  grade 3 systemic flu-like symptoms,
- Grade 3 or 4 febrile neutropenia
- Grade 3 or 4 thrombocytopenia with bleeding
- $\geq$  grade 3 non-hematologic and grade 4 hematologic toxicities, or
- Death
- Exceptions include
  - Asymptomatic laboratory abnormalities
  - Grade 3 fatigue
  - Grade 3 dermatologic AEs that are considered mild in severity but only considered grade 3 because of  $>30\%$  body surface involvement (rash, pruritus, etc.)
  - Fever, chills rigors, hypertension, hypotension, syncope, or hypoxia that resolve within 24 hours of intervention
  - Diarrhea, nausea or vomiting that resolves to  $<$  grade 3 within 24 hours of intervention
  - Grade 3-4 hyperglycemia or grade 3 hypophysitis where symptoms are controlled on hormone replacement therapy

Patients will be observed for DLTs for 28 days after the first dose of Helixor® M. Patients who experience a DLT will be discontinued from study treatment. Any patient who receives  $< 75\%$  of the scheduled doses during the DLT period but does not experience a DLT will be replaced.

This phase I study will evaluate up to 8 dose levels of Helixor® M as a single agent: 150 mg, 300 mg, 600 mg, 900 mg, 1200 mg, 1500 mg, 1800 mg, and 2000 mg. Dose escalation

will proceed using an accelerated titration design.

Patients will be assigned to a dose level in the order of study entry. The first cohort of 1 subject will receive mistletoe at the 150 mg dose level. One subject will be enrolled in each cohort until a subject experiences a drug-related toxicity of grader 2 or higher, whereupon an additional 2 patients will be enrolled at that dose level. Thereafter, the traditional 3+3 design will be instituted as described below, with 3 or 6 patients treated at this dose level and at all subsequent dose levels depending upon the incidence of DLTs.

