The target DLT rate is  $< 33\%$ . The MTD will be defined as the dose of Helixor® M in which  $< 2$  of 6 patients experiences a dose limiting toxicity (DLT) with the next higher dose having at least 2 of 3 or 2 of up to 6 patients experiencing a DLT. A subject who is withdrawn from the study prior to completion of the DLT period for a reason other than a DLT and has not experienced a study drug-related adverse event of  $\geq$  grade 2 may be replaced.

Once the MTD (or maximum administered dose if no MTD is determined) has been defined, an additional 10 patients will be enrolled and treated at that dose level in an expansion phase (for a total of 16 patients treated with the MTD) to further characterize safety and obtain preliminary estimates of efficacy.

Continuous evaluation of toxicity events in the expansion cohort will be performed throughout enrollment. If the rate of toxicities meeting DLT criteria appears to be higher than 30%, we will temporarily halt the study pending dose modification. Specifically, we will apply a Bayesian toxicity monitoring rule that suspends the enrollment if the posterior probability of risk being larger than 0.3 is 75% or higher.

We expect the SAE rate is about 27%. The monitoring rule uses  $\text{beta}(2, 5.5)$  as a prior distribution. This means that our prior guess at the proportion of toxicity is 27%, and there is 90% probability that this proportion is between 6% and 55%.

The decision rule for safety stopping is as follows:  
Stop if:

|        |   |   |   |    |
|--------|---|---|---|----|
| # AE   | 2 | 3 | 4 | 5  |
| Out of | 2 | 3 | 6 | 9  |
|        |   | 4 | 7 | 10 |
|        |   | 5 | 8 |    |

For example, if two out of the first 2 patients have adverse events, we will stop the accrual. If three or more out of the first 3-5 patients have adverse events, we will stop.

The operating characteristics of the stopping rule are shown below and are based on 5000 simulations:

| True AE rate | % Simulated trials declaring unsafe | Average sample size (out of 10) |
|--------------|-------------------------------------|---------------------------------|
| 0.10         | 5.1                                 | 9.7                             |
| 0.20         | 10.8                                | 9.4                             |
| 0.25         | 17.9                                | 9.1                             |
| 0.30         | 28.9                                | 8.5                             |

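### The expansion stopping-rule table assumes each outcome is known before the next patient enrols; the plan neither ensures this nor says how patients under observation count, and the 0.10 row is wrong even so

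*Protocol*

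**What the plan says.** Protocol section 13.1 provides that, once the dose is chosen, "an additional 10 patients will be enrolled and treated at that dose level in an expansion phase". On monitoring it says: "Continuous evaluation of toxicity events in the expansion cohort will be performed throughout enrollment". The rule "suspends the enrollment if the posterior probability of risk being larger than 0.3 is 75% or higher", with a beta(2, 5.5) prior. The resulting boundary is 2 of 2, 3 of 3 to 5, 4 of 6 to 8 and 5 of 9 to 10. It is illustrated by order of entry: "if two out of the first 2 patients have adverse events, we will stop the accrual", and "If three or more out of the first 3-5 patients have adverse events, we will stop".

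A table follows with the percentage of trials declared unsafe and the average sample size at seven true rates. It is introduced by "The operating characteristics of the stopping rule are shown below and are based on 5000 simulations". No accrual or outcome-timing assumption is given for these simulations.

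Two DLT windows appear. Section 5.4 says "Patients will be observed for DLTs for 28 days after the first dose of Helixor® M". Section 13.1 instead follows patients through their first three doses at the full assigned level, which on the section 5.1 schedule ends about day 8 (lead-in Monday, then Wednesday, Friday, Monday). Section 13.2 has accrual rate in its heading but gives none.

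**The concern.** The table is the protocol's statement of how well the expansion patients are protected. Its two columns say how often an unsafe dose would be flagged and how many patients would be treated first.

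Continuous monitoring in a multi-centre study, with no minimum gap between patients, can leave several patients under observation together. A count out of n can then mean three things: the first n in order of entry, those whose outcome is known, or all enrolled. These are different rules. Counting events at once but non-events only at window end makes events visible sooner and raises false stops. Counting all enrolled patients treats pending patients as event-free in the denominator and weakens the rule. Even the order-of-entry reading lets more patients start treatment before a boundary crossing is seen.

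**Working it through.** **Inputs (Protocol 13.1).** Prior beta(2, 5.5); stop if Pr(risk > 0.3) ≥ 0.75; 10 patients. The monitored event is taken to be a toxicity meeting DLT criteria, as the rule's introduction says.

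**1. Boundary.** After k events in n patients the posterior is beta(2 + k, 5.5 + n − k). For 2 of 2, Pr(risk > 0.3) = 0.77; for 2 of 3 it is 0.69 and for 3 of 3 it is 0.88. Continuing to n = 10 reproduces the printed boundary at every n from 2 to 10.

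**2. Printed table, outcomes known one at a time.** Counting the paths that first cross the boundary at each n, with q = 1 − p:

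- a2 = p²; a4 = 2p³q; a5 = 5p³q²; a7 = 9p⁴q³; a8 = 23p⁴q⁴; a10 = 43p⁵q⁵ (no first crossing is possible at n = 3, 6 or 9)
- P(declared unsafe) = a2 + a4 + a5 + a7 + a8 + a10
- Average sample size = 10 − 8·a2 − 6·a4 − 5·a5 − 3·a7 − 2·a8

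At p = 0.30: 0.0900 + 0.0378 + 0.0662 + 0.0250 + 0.0447 + 0.0176 = 0.281. The average is 10 − 0.720 − 0.227 − 0.331 − 0.075 − 0.089 = 8.56.

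| True rate | Printed | Exact sequential |
|---|---|---|
| 0.10 | 5.1% / 9.7 | 1.83% / 9.88 |
| 0.20 | 10.8% / 9.4 | 10.54% / 9.42 |
| 0.25 | 17.9% / 9.1 | 18.31% / 9.04 |
| 0.30 | 28.9% / 8.5 | 28.12% / 8.56 |
| 0.35 | 39.8% / 8.0 | 39.37% / 8.00 |
| 0.40 | 51.6% / 7.4 | 51.23% / 7.38 |
| 0.45 | 62.8% / 6.7 | 62.82% / 6.73 |

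Rows 0.20 to 0.45 agree within 0.8 points and 0.1 patients, and none is more than 1.3 Monte Carlo standard errors away. At 0.10 the standard error is √(0.0183 × 0.9817 / 5000) = 0.0019, so the gap is (0.051 − 0.0183) / 0.0019, about 17 standard errors. At p = 0.15 the formula gives 5.08% and 9.70, which is the printed pair.

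**3. Overlapping windows.** Assumptions not in the documents: exponential gaps with mean 28, 14 or 7 days (1, 2 or 4 patients per 28 days) and event times uniform within the window. Several thousand simulated trials were run per setting.

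*Order of entry, rechecked at each event, pending patients event-free until shown otherwise.* A crossing occurs exactly when the sequential rule would cross, so the stopping probability is unchanged (about 28% at 0.30, 63% at 0.45). Average enrolled at 0.45, printed 6.7:

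- 28-day window: about 7.0 to 7.1 at 1 patient per 28 days, 7.3 at 2, 8.0 at 4
- 8-day window: 6.8 to 7.1 across the same range

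With the 28-day window and 4 patients per 28 days, enrolment halts before the tenth patient in about 49% of trials. The sequential figure is 62.8% − a10 (4.0%) = 58.8%. If the rule also waits for completed windows, the average in that setting is 8.76.

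*Other denominators at 0.30 (printed 28.9% / 8.5), as % declared unsafe / average enrolled:*

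| Window, mean gap | Evaluated patients only | All enrolled |
|---|---|---|
| 28 d, 28 d | 31.2 / 8.53 | 25.8 / 8.82 |
| 28 d, 14 d | 35.8 / 8.41 | 22.6 / 9.11 |
| 28 d, 7 d | 42.8 / 8.42 | 18.9 / 9.48 |
| 8 d, 28 d | 29.4 / 8.51 | 27.8 / 8.61 |
| 8 d, 14 d | 30.2 / 8.53 | 26.3 / 8.72 |
| 8 d, 7 d | 31.8 / 8.50 | 24.4 / 8.93 |

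**The case against.** A reader might infer that overlapping windows as such invalidate the printed error rates. The documents do not support that. The worked example in 13.1 speaks of the first 2 and the first 3 to 5 patients, which is order of entry, and under that count the stopping probabilities are the sequential ones however fast patients arrive. The 19% and 43% figures need denominators that the example does not suggest.

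Nor can one say that no counting rule gives both printed columns. With the short window and one patient per 28 days, counting evaluated patients gives 29.4% and 8.51 at 0.30, against the printed 28.9% and 8.5.

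The size also rests on assumed accrual and event timing. The reactions listed in sections 2.1 and 7.6 are largely allergic or infusion-type. If events fall in the first 8 days of a 28-day window, order of entry gives averages of only 6.9 to 7.1 at 0.45. Bi-weekly safety meetings (12.2) and Safety Monitoring Committee oversight (12.3) add protection, and the handling of pending patients is often left to an SAP, which is not shown here.

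All of this limits the size, and most of it stands. It does not remove the point. The protocol itself fixes the rule and prints its performance, so the assumption behind those figures belongs beside them. The example favours order of entry, but the table headings and the promise of continuous evaluation leave pending patients undefined. None of it touches the 0.10 row.

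**Conclusion.** The point holds in limited form. The one firm numerical error is the 0.10 row, which overstates stopping (5.1% against 1.8%) and understates average enrolment (9.7 against 9.88); it looks like the result for 0.15. The remaining rows are sound for fully sequential outcomes, an assumption that the protocol neither states nor enforces.

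Under the order-of-entry reading only the average-sample-size column suffers. At 0.45 the excess over 6.7 is about 0.3 to 1.3 patients with the 28-day window and 0.1 to 0.4 with the 8-day window. Under the other two readings the stopping probability also shifts, by up to 14 points upward or 10 downward at 0.30 in the most crowded setting examined, and by little with slow accrual or the short window. These sizes depend on the assumed 1 to 4 patients per 28 days, uniform event times, and which of the two windows governs the expansion cohort. The row error and the missing counting rule do not depend on them.

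**What to change.** In section 13.1:

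- State that the boundary applies to the first n patients in order of entry and is rechecked at each event, with a pending patient counted as event-free until an event or the end of the window. This keeps the stopping probabilities for 0.20 to 0.45.
- State the outcome-timing assumption behind the table, and re-simulate the average-sample-size column for the planned accrual rate, given in section 13.2.
- Correct the 0.10 row to 1.8% and 9.9, or relabel it 0.15 if that was the rate simulated.
- Reconcile the DLT windows in sections 5.4 and 13.1 and say which one the expansion monitoring uses. Which is right is for the sponsor to settle.

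The cost is a few sentences, one corrected row and one re-simulated column that will look slightly less favourable. The boundary and the number of patients do not change.

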### 13.2 Sample Size/Accrual Rate

The phase I dose escalation study will require a minimum of 3 patients and a maximum 48 of patients. The expansion phase will evaluate 16 patients total including the 6 patients that are treated at MTD or maximum administered dose in dose escalation portion.

### 13.3 Analysis of Primary/Secondary Endpoints

The primary objective is to determine the safety, to characterize the toxicity profile of Helixor® M administered IV in patients with advanced solid tumors and to identify the maximum tolerated dose (MTD). Safety assessment measures of toxicity and adverse events will be tabulated by type and grade and will be objectively reviewed to determine the safety and tolerance of Helixor® M. The MTD will be defined as the dose of Helixor® M in which < 2 of 6 patients experiences a dose limiting toxicity (DLT) with the next higher dose having at least 2 of 3 or 2 of up to 6 patients experiencing a DLT.

In the expansion cohort, we will estimate the objective response rate (ORR) for the 16 patients. If we observe 3 responses (19%), the corresponding 90% confidence interval is [7%, 39%].

Secondary endpoints will be to measure tumor marker dynamics in patients receiving treatment. Tumor marker dynamics will be presented with summary statistics and boxplots.

Exploratory objectives will be to 1) to estimate PFS and TTP in patients treated with Helixor® M at MTD or maximum administered dose if no MTD is determined, and to measure tumor marker dynamics in patients receiving treatment, 2) collect peripheral blood mononuclear cells (PBMCs) and serum to explore potential therapeutic targets, biomarkers, and predictors of treatment response, 3) assess tumor burden dynamics using exploratory circulating biomarkers in serial collections of sera and plasma at baseline and throughout treatment, 4) collect pre and post-treatment whole blood to evaluate germline mutations in circulating DNA that may correlate with clinical benefit, and 5) determine changes in cytokine production by peripheral blood mononuclear cells (PBMC) as indicated by interleukin 2 [IL-2], interleukin 6 [IL-6], interleukin 8 [IL-8], interleukin 12 [IL-12], and interferon- gamma [IFN-γ]. PFS and TTP will be analyzed as time-to-event outcomes, for which we can estimate event-time distributions using the Kaplan-Meier method. PFS will be calculated as the time from start of treatment to time of progression per RECIST 1.1 and irRC or death, whichever occurs first. If the subject does not have a documented date of progression or death, PFS will be censored at the date of the last adequate assessment. Patients who start any subsequent anti-cancer therapy without a prior reported progression will be censored at the last evaluable tumor assessment prior to initiation of the subsequent anti-cancer therapy. TTP is the time from start of treatment to time of progression per RECIST 1.1 and irRC.

We will examine the correlation between potential therapeutic targets/biomarkers/predictors of treatment response and clinical endpoints. For time-to-event clinical endpoints, the potential predictors will be treated as covariates (time-varying or not) in Cox proportional-hazard models. For other clinical endpoints, we will use generalized estimating equations (GEE) to analyze the correlation between the potential predictors and clinical endpoints. Summary statistics and boxplots will be used to present the levels of potential predictors at each time point, assess tumor burden dynamics, compare pre and post-treatment germline mutations in circulating DNA, and examine the changes in cytokine production by PBMC.

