### **1.3 Exploratory Objectives**

- 1.3.1 To estimate progression-free survival (PFS) and time to progression (TTP) in patients treated with Helixor® M mistletoe extract using RECIST 1.1 and irRC.
- 1.3.2 To collect peripheral blood mononuclear cells (PBMCs), serum, and plasma to explore potential therapeutic targets, biomarkers, and predictors of treatment response (PFS and best overall response).
- 1.3.3 To assess tumor burden dynamics using exploratory circulating biomarkers in serial collections of sera and plasma at baseline and throughout treatment.
- 1.3.4 To collect pre and post-treatment whole blood to evaluate germline mutations in circulating DNA that may correlate with clinical benefit (PFS and best overall response).
- 1.3.5 To determine changes in cytokine production by peripheral blood mononuclear cells (PBMC) as indicated by interleukin 2 [IL-2], interleukin 6 [IL-6], interleukin 8 [IL-8], interleukin 12 [IL-12], and interferon- gamma [IFN-γ].

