### **9.3 Plasma Studies**

Baseline and post-treatment plasma will be collected to assess tumor burden dynamics using exploratory circulating biomarkers, as well as to evaluate germline mutations in circulating DNA that may correlate with clinical benefit. Whole blood (up to 20 ml) will be collected at the designated time points in a 10 ml plasma preparation tubes with EDTA (PPT, BD Vacutainer, Franklin Lakes, NJ) and gently swirled to mix blood with EDTA. Within three hours of collection, the sample will be processed using standard procedures for plasma separation. Plasma will be divided into 1 ml aliquots and stored at -80°C. Pellets from this separation procedure will also be stored at -80°C. Please see the Laboratory Manual for further details.

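### The planned pre/post-treatment comparison of germline mutations in circulating DNA carries no information, because germline genotype does not change within a patient

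*Protocol*

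**What the plan says.** Three sections of the protocol deal with this measure, and all three call it germline.

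- Section 1.3, objective 1.3.4: "To collect pre and post-treatment whole blood to evaluate germline mutations in circulating DNA that may correlate with clinical benefit". The objective specifies clinical benefit as PFS and best overall response.
- Section 9.3: baseline and post-treatment plasma is collected for tumor burden dynamics, "as well as to evaluate germline mutations in circulating DNA that may correlate with clinical benefit".
- Section 13.3 repeats the objective and then, in its closing sentence on descriptive methods, says that summary statistics and boxplots will be used, among other things, to "compare pre and post-treatment germline mutations in circulating DNA".

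Section 13.3 also plans association models for biomarkers in general. For time-to-event endpoints, "the potential predictors will be treated as covariates (time-varying or not) in Cox proportional-hazard models". For other endpoints, "we will use generalized estimating equations (GEE) to analyze the correlation between the potential predictors and clinical endpoints".

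No section names somatic or tumor-derived mutations. Section 9.3 notes that "Pellets from this separation procedure will also be stored at -80°C" and leaves further detail to the Laboratory Manual, which is not part of the protocol text.

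**The concern.** A pre/post comparison makes sense for a quantity that treatment, or the course of disease under treatment, can alter. Germline genotype is not such a quantity. The comparison therefore has nothing to estimate, and a change score that is zero for everyone cannot correlate with an outcome.

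The wording is the same in the objective, the sample section and the analysis section, so no other part of the protocol corrects it. An analysis plan that followed section 13.3 would inherit the empty comparison. What is at stake is a misleading exploratory result: a discordant genotype call between two samples from one patient could be reported as a change under treatment. The sentence that plans this comparison is also the only analysis sentence that names these mutations, so a reader looking for the analysis of objective 1.3.4 finds the uninformative one first.

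**Working it through.** The protocol gives no sample size, power, error rate or effect size for this analysis, so there is no figure to reproduce. The check is logical, followed by an illustration under a stated assumption.

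**Step 1. The contrast.** Let G be a patient's germline status for a variant (carrier or not). G is the same before and after treatment, so post − pre = G − G = 0. The mean change is 0 and its variance is 0, at any sample size.

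**Step 2. What the objective asks.** Objective 1.3.4 asks whether G is associated with PFS and best overall response. That is a between-patient question. It needs variation in G across patients, which exists whenever some carry the variant and others do not. It needs no variation within a patient. One baseline determination supplies all the information on G, and a second one adds only a check of the assay.

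**Step 3. What an observed change would mean.** Suppose each sample's call is wrong, independently, with probability e. A pre/post pair disagrees when exactly one of the two calls is wrong:

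d = 2e(1 − e)

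For n patients the expected number of discordant pairs per variant is n·d, and P(at least one) = 1 − (1 − d)^n.

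Inputs:
- n = 16: patients in the expansion phase, including the 6 treated at that dose during escalation (section 13.2).
- n = 58: the stated maximum of 48 in escalation plus the 10 additional expansion patients (sections 13.1 and 13.2).
- e = 0.1%, 1% and 2%: assumptions; the protocol states no calling error.

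For e = 1%: d = 2 × 0.01 × 0.99 = 0.0198. With n = 16 the expected number is 16 × 0.0198 = 0.32, and P(at least one) = 1 − 0.9802^16 = 0.27.

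| Assumed error e | d | Expected pairs, n = 16 | P(≥ 1), n = 16 | Expected pairs, n = 58 | P(≥ 1), n = 58 |
|---|---|---|---|---|---|
| 0 | 0 | 0 | 0% | 0 | 0% |
| 0.1% | 0.002 | 0.03 | 3% | 0.12 | 11% |
| 1% | 0.0198 | 0.32 | 27% | 1.15 | 69% |
| 2% | 0.0392 | 0.63 | 47% | 2.27 | 90% |

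These figures are per variant. Every discordance they count is false by construction, so the table describes the quality of the assay and says nothing about the treatment.

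**The case against.** Four arguments can be made for the plan as it stands.

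**The objective is not about change.** It asks for association with PFS and best overall response, and the Cox and GEE models can provide that. The Cox wording expressly allows covariates that do not vary in time, so baseline germline status fits. This stands. A reader might infer from the empty comparison that objective 1.3.4 cannot be answered; the protocol does not support that. The models do not rescue the comparison itself, however, and they need only one sample per patient.

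**The readout could be quantitative.** The sentence begins "Summary statistics and boxplots will be used to present the levels of potential predictors at each time point", and boxplots suit a continuous measure. Measured allele fractions in circulating DNA can shift as the tumor-derived share of that DNA shifts. This stands in part: a true change of exactly zero holds for genotype, not for every quantity an assay might report. But the protocol specifies no such measure, and a shift of that kind would reflect tumor DNA and not a change in the germline.

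**The blood is used anyway.** Section 9.3 collects the same plasma for tumor burden dynamics under objective 1.3.3, where serial sampling is needed, and the study calendar reserves no draw for germline work. This stands in full. It would be wrong to infer that the serial draws are wasted.

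**Somatic variants were obviously meant.** Circulating DNA, paired sampling and the neighboring tumor-burden aim all make this plausible. It remains an inference, since no section says so. If it is right, the wording is wrong in three places; if it is wrong, the pre/post comparison should go.

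**Conclusion.** The point holds for the pre/post comparison named in section 13.3 and for the paired sampling attached to the germline measure in objective 1.3.4 and section 9.3. As written, the comparison yields no information on treatment: the true within-patient change in genotype is zero, and anything observed would be calling error or a sample mix-up. This conclusion rests only on the meaning of germline. The error percentages in the illustration are assumptions and serve only to show that a false change need not be rare.

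The point goes no further than that. The association question can still be analysed with the planned models, provided that germline variants count among the potential predictors, which is the natural reading of section 13.3. Low priority is appropriate: this is one of several exploratory aims, handled descriptively, and it does not touch the MTD, safety monitoring or sample size.

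**What to change.** Reconcile objective 1.3.4, section 9.3 and section 13.3 in one of two ways, or both. The choice depends on what was intended, which the sponsor must state.

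(a) If tumor-derived variants were meant: replace germline with somatic (tumor-derived) variants in plasma DNA in all three places, compare those pre versus post, and use the stored pellets to separate out germline variants.

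(b) If germline variants were meant: delete the pre/post comparison from section 13.3, remove the paired sampling for this purpose from objective 1.3.4 and section 9.3, and say that germline status from one baseline sample enters the planned Cox and GEE models as a fixed covariate.

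The cost is small. Both routes need wording changes and a check that the consent text covers the testing finally chosen. Route (a) may add some assay work, on samples that the protocol already collects and stores. Neither route changes the collection schedule, since the serial plasma remains needed for objective 1.3.3.
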